**Methods/Design:**

This is a cluster randomized trial. A total of 800 high-CVD-risk patients attending diabetes and hypertension clinics at health centers in Muang District, Chiang Rai province, Thailand, will be studied with informed consent. A health center recruiting 100 participants is a cluster, the unit of randomization. Eight clusters will be randomized into intervention and control arms and followed up for 1 year. Within the intervention clusters the following will be undertaken: (1) salt content in the daily diet will be measured and shown to study participants; (2) 24-hour salt intake will be estimated in overnight-collected urine and the results shown to the participants; (3) a dietician will assist small group health education classes in cooking meals with less salt. The primary outcome is blood pressure change at the 1-year follow-up. Secondary outcomes at the 1-year follow-up are estimated 24-hoursalt intake, incidence of CVD events and CVD death. The intention-to-treat analysis will be followed.

Blood pressure and estimated 24-hour salt intake will be compared between intervention and control groups at the cluster and individual level at the 1-year follow-up. Clinical CVD events and deaths will be analyzed by time-event analysis. Retinal blood vessel calibers of CVD-risk patients will be assessed cross-sectionally. Behavioral change to reduce salt intake and the influencing factors will be determined by structured equation model (SEM). Multilevel regression analyses will be applied. Finally, the cost effectiveness of the intervention will be analyzed.

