### Design

This is a cluster randomized controlled trial (CRT). The rationale for choosing a CRT design is to prevent contamination by sharing second-hand massage between participants of intervention and control arms. Instead of randomizing the individual patient, clusters of eligible patients will be randomly allocated into the intervention and control arms. There will be two arms of CRT: the salt reduction intervention arm and control arm. The units of randomization are health centers.

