### Sample size

For a conventional randomized control trial, a total of 240 participants, randomizing 120 into each arm, will have enough power (90%) to detect the minimal difference of systolic blood pressure 130 (±20) and 120 (±20) mmHg, diastolic pressure 90 (±20) and 80 (±20) mmHg, difference in 24-hour estimated salt intake 10 (±5) and 8 (±4) g/day and CVD event rate of 0.15% and 0.08% between the control and intervention group with a 95% confidence interval
[6,31]. The cluster randomized trial design used in RESIP-CVD might result in loss of power and reduced efficiency. In this cluster randomized trial, the number of participants in each cluster will be the same, and other variable factors such as geography, food tradition, race and dietary habits are assumed not to be different for delineating the intracluster coefficient. To compensate the design effect, the inflation factor has been calculated by the formula (*Deff* = 1 + (*m–1*)*ρ*) where *Deff* is inflation factor for design effect, *m* is the size of each cluster, which is 30 and *ρ* is the intracluster coefficient which is assumed to be 0.07. The sample required for a cluster randomized trial was inflated to 720. With a loss to follow-up of approximately 10%, we expect that the sample size of 800 patients will yield sufficient power to detect the desired minimal difference in primary and secondary outcomes between the intervention and control group. All eight clusters of the RESIP-CVD study will enroll 100 eligible participants.

We identified the confounders and planned to collect the information for multivariate analysis adjustment. (Table
4)

**Table 4 T4:** Confounder measurements

**Confounder**	**Variables**	**How to measure**
Demographic characteristics	Age, sex, social status, family size, educational attainment, occupational history, income	Questionnaire
Lifestyle	Smoking, alcohol	Questionnaire
Genetic factor	Family history of diabetes/hypertension	Questionnaire
Drugs	Different medications for diabetes and hypertension	Clinical record

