### Analysis plan

The intention-to-treat analysis will be followed. The mean blood pressure and mean daily salt intake of both the intervention and control arms will be compared at the individual level at the 1-year follow-up using Student’s *t* test or the non-parametric test based on distribution. The analysis will be carried out at both the cluster and individual levels. The CVD incidence rate will be compared by time-to-event analysis. A structural equation modeling analysis will be used to determine the behavioral change predictors. Information such as the self-efficacy, stage of attitudinal change, decisional balance, family support, health center support, ready-made meals usage and cooking utensils will be collected by questionnaires and analyzed by the SEM (Figure
4).

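### The only test named for blood pressure and salt intake ignores health-centre clustering, and the plan does not say whether it or a cluster-respecting analysis decides

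*Protocol article*

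**What the plan says.** On the design, the protocol article is clear: "The units of randomization are health centers" (Design). There are four centres per arm with 100 participants each (Study site). The Sample size section assumes an intracluster coefficient of 0.07 and inflates the sample for clustering.

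On the analysis, three statements bear on blood pressure, the primary outcome:

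- Analysis plan: mean blood pressure and mean daily salt intake "will be compared at the individual level at the 1-year follow-up using" Student's t test or a non-parametric test, depending on distribution.
- Analysis plan, next sentence: "The analysis will be carried out at both the cluster and individual levels". No cluster-level method is given.
- Abstract, Methods/Design: blood pressure and salt intake are to be compared at cluster and individual level at one year. Later in the same paragraph, after a sentence on behavioural change, it adds: "Multilevel regression analyses will be applied". No outcome is attached to that line, and the Analysis plan does not repeat it.

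No section names one of these as the decisive analysis, and none says that the individual-level test is adjusted for clustering.

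**The concern.** A two-sample t or rank test on individuals treats about 720 to 800 patients as independent. They are not independent in this design: patients of one centre share a treatment assignment made once for the whole centre, and the sample size itself supposes that their outcomes are correlated. The test therefore uses too small a standard error for the difference between arms.

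The second problem is the open choice. With eight centres, an unadjusted individual-level result and a cluster-level result can easily disagree. Where no analysis is designated in advance, the one with the inflated error rate is free to support the claim of effectiveness. This is a method stated in the article, not a detail left for a fuller document, and an analysis plan written to follow this text would carry it forward.

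**Working it through.** **Inputs.** Four centres per arm and 100 per centre (Study site). Intracluster coefficient ρ = 0.07, 10% loss to follow-up, and "systolic blood pressure 130 (±20) and 120 (±20) mmHg", that is a 10 mmHg difference with SD 20 (Sample size). The significance level is read as 5% from "between the control and intervention group with a 95% confidence interval"; sidedness is not stated and is taken as two-sided. With 10% loss, about 90 patients per centre are analysed.

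**The plan's own figures.** The article uses a cluster size of 30 in its design effect:

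- Deff = 1 + (30 − 1) × 0.07 = 3.03
- 240 × 3.03 = 727, against the stated 720 (exactly 240 × 3 if Deff is rounded)
- 720 / 0.90 = 800, as stated

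The sample size therefore reproduces. The article states no error rate for the t test. The cluster size of 30 against 100 actually enrolled is a separate matter; the analysis will face the real cluster size, so that is used below.

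**False-positive rate of the unadjusted test.** With equal clusters, the true variance of the difference in means is Deff times the variance that the test uses. So

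rate = 2 × (1 − Φ(1.96 / √Deff)), with Deff = 1 + (m − 1)ρ.

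| ρ | m | Deff | Rate |
|---|---|---|---|
| 0.07 | 90 | 7.23 | 46.6% |
| 0.07 | 100 | 7.93 | 48.6% |
| 0.05 | 90 | 5.45 | 40.1% |
| 0.02 | 90 | 2.78 | 24.0% |
| 0.01 | 90 | 1.89 | 15.4% |
| 0.005 | 90 | 1.45 | 10.3% |

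At ρ = 0.07 and m = 90, the standard error is understated by √7.23 = 2.69.

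**Check by simulation** (four centres against four, no true effect, ρ = 0.07; 30,000 trials for the t tests, 6,000 for the rank test):

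| Test | m = 90 | m = 100 |
|---|---|---|
| Individual-level t | 47.2% | 48.3% |
| Individual-level rank | 46.5% | 48.5% |
| t on 8 centre means, 6 df | 5.0% | 4.8% |

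The non-parametric option is no protection. The cluster-level t test holds its level; with equal cluster sizes and normal centre means it is exact at any ρ.

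**What the valid test can detect** (SD 20, ρ = 0.07, m = 90, so 360 patients per arm):

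- Unadjusted standard error = √(2 × 400 / 360) = 1.49 mmHg; 95% half-width 1.96 × 1.49 = 2.9 mmHg
- Correct standard error = √(2 × 400 × 7.23 / 360) = 4.01 mmHg; with 6 df, half-width 2.447 × 4.01 = 9.8 mmHg
- Noncentrality for 10 mmHg = 10 / 4.01 = 2.49, which gives power of 55% (56% with m = 100)

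**The case against.** The strongest reply is that the article does not make the individual-level test the primary comparison. The sentence that follows it extends the analysis to the cluster level and can fairly be read as the same comparison run at both levels, which would include a t test on centre means. The abstract ties a cluster-level comparison to blood pressure explicitly and adds multilevel regression. Table 4 lists confounders for multivariable adjustment. On this view a valid analysis is already planned, and the rest is detail for a statistical analysis plan.

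Much of this stands. A reader might infer that the trial's primary conclusion has a 47% false-positive rate. The documents do not support that, because no passage makes the unadjusted test decisive. The 47% also belongs to an assumed planning coefficient; at lower values the inflation is smaller.

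What the reply does not do is remove the named test. The cluster-level analysis has no method, the multilevel line has no outcome, and adjustment for individual confounders does not account for correlation within centres. The article still presents an invalid test as an analysis of the primary outcome, alongside valid ones and without ranking them.

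A reader might also extend the point to cardiovascular events. The article says only that incidence will be compared by time-to-event analysis. Nothing wrong is stated there, and the details may properly sit in a fuller document, so the point is not pressed.

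**Conclusion.** The point holds in conditional form. The only test specified for blood pressure and salt intake is not valid for a trial that randomises eight centres, and the plan leaves open whether that test or a cluster-respecting analysis decides. If the named test decides, a nominal 5% test rejects a true null in about 47% of trials at the protocol's coefficient of 0.07. Even at 0.005, one-fourteenth of that value, the rate is about double the nominal level.

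These figures assume a two-sided 5% test, equal cluster sizes, loss to follow-up spread evenly over centres, and a coefficient of 0.07 that applies to one-year blood pressure. Because the validity of the primary conclusion turns on this choice, it should be settled before outcome data are analysed.

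**What to change.** Designate one primary analysis of blood pressure that respects clustering. Either of these would do:

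- a t test on the eight centre summaries, with 6 degrees of freedom; or
- a linear mixed model on individuals with a health-centre random intercept and small-sample degrees of freedom (Kenward-Roger or Satterthwaite).

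Remove the unadjusted individual-level t and rank tests as inferential analyses; individual-level means may stay as description. Apply the same rule to salt intake, and tie the abstract's multilevel line to an outcome or drop it.

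No new data are needed, and the article gives the trial status as still recruiting. The change is not free, however. Intervals become wider, and the plan must acknowledge that the valid test has about 55% power for 10 mmHg (SD 20, coefficient 0.07). The 90% in the Sample size section is given for an individually randomised trial of 240, and the article expects the inflated sample to preserve sufficient power. That shortfall comes from the design; the corrected analysis only makes it visible.

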**Figure 4 F4:**
[figure not shown]
Path model to analyze predictors of behavioral change by structural equation modeling (SEM).

Differences in CVD events and deaths and the associated costs between intervention and control groups will be estimated for up to 10 years after the intervention. Lifetime costs and health outcomes for our study population (aged 35 years and above) will be estimated using data both in and outside of Thailand. Outcomes of the analysis will be: CVD events and deaths averted and the cost over 10 years, incremental cost-effectiveness ratio (ICER) per CVD death averted, lifetime costs and quality-adjusted life years (QALYs) gained and ICER per QALYs gained. The analysis will be performed using a societal perspective. All the future costs and outcomes will be discounted at a rate of 3% per annum. Sensitivity analysis will be employed to check the robustness of the results. Budget impact analysis will be applied. From a government perspective, the direct medical cost of CVDs will be estimated both with and without special health education in Chiang Rai Province in the course of the next 10 years in order to assess its impact on the Universal Health Coverage Scheme budget.

## Discussion

There have been many previous studies related to salt reduction interventions
[33]. This current study is unique as the study population is exclusively composed of high-CVD-risk patients stratified by applying the universal Framingham general CVD risk scoring system. Therefore, the intervention can be prioritized, focusing on the high-risk individuals most vulnerable to CVD morbidity and mortality at the community level within a developing setting. The intervention will not merely be a case of counseling and providing information, however. The intervention group will be able to clearly see and understand the salt level content in their daily food and their estimated daily salt intake following urinary salt measurement. Furthermore, we will use equipment which is affordable within developing settings to visualize the salt content in food and the patient’s urine. The effectiveness of the salt reduction intervention will be assessed by multiple outcomes (Table
3).

In many previous clinical studies, reduced salt intake has been shown by means of urinary sodium measurement in urine collected over a period of 24-hours
[8,34]. In the current study, overnight urine will be collected and assessed for urinary sodium
[23,35]. This is a more feasible and practicable outcome measurement that overcomes the possible bias caused by under-collection of urine. In addition, we will assess the blood pressure changes comparatively between participants in the intervention and control groups. The reported incidence of CVD events and deaths will be compared to determine the clinical effectiveness of the health promotion intervention.

Health system costs and reimbursement systems differ between developing and developed countries. Thailand is a middle-income country in Southeast Asia, with 100% insurance coverage for non-communicable disease-related services. It is estimated that by allocating just US$ 0.06 per person for voluntary salt reduction, 310,000 deaths can be prevented over a 10-year period
[36,37]. WHO has recommended salt reduction in addition to risk modification by advocating multiple-drug treatments using, for example, anti-hypertensive, oral hypoglycemic agents and lipid-lowering medications. It is necessary to determine whether the prevention of CVD incidence by a salt reduction strategy is cost-effective in terms of treatment and health service costs compared to traditional drug treatment that has little concern for lifestyle modification
[38]. The cost-effectiveness analysis of our study is expected to answer these questions for developing countries.

We have designed the study to have minimal residual confounding factors and selected practical and contemporary approaches that overcome hard-to-achieve lifestyle modifications. Thus, we expect that implementing a health promotion intervention trial in a practical setting will yield comprehensive and applicable evidence for global reduction of CVD deaths and prevention of CVD events.

### Trial status

Recruiting participants.

## Abbreviations

CRT: Cluster randomized trial; HC: Health center; FMH scoring: Framingham general CVD risk scoring; CVD: Cardiovascular disease; NSAID: Nonsteroidal antiinflammatory drug; SEM: Structural equation modeling; ICER: Incremental cost-effectiveness ratio; QALYs: Quality-adjusted life years.
